## Methods/Design

### Study aims

The Andromeda study was designed with two main aims: *1)* to define appropriate women risk-based stratifications for personalized screening considering different criteria such as: a model-based risk estimate of absolute BC risk including reproductive, BC family and biopsy history, breast density, lifestyle habits and *2)* to evaluate whether selected circulating miRNAs, previously associated to BC, are significantly altered in the plasma of cancer patients compared to matched healthy controls; and also if they satisfy pre-specified true and false positive rates, considered minimally acceptable in the screening setting.

In order to define groups of women characterized by different BC risk, the above mentioned criteria will be assessed and compared in terms of positive predictive value (PPV), either when considered alone or in combination. Related to the first main aim, secondary objectives are: to measure risk group-specific screening indicators (i.e., detection rate, recall rate and benign/malignant surgical biopsy ratio); to quantify the impact of tailored screening interventions on health outcomes; to evaluate the economic and organizational feasibility of these interventions.

With regards to the second main aim, secondary objectives are: to assess the tumor characteristics associated with miRNA levels in case subjects to understand the role of these biomarkers in cancer detection; to assess the association between the investigated BC risk factors and miRNA levels in the control group to define different thresholds for screening positivity; to evaluate the presence of 77 established SNPs associated with BC risk [18] and their impact on BC score calculation.

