### Study setting

The eligible population of the study consists of 46–67-year-old women invited to breast screening in the cities of Turin and Biella (two Northern Italian cities in Piedmont), where BC screening is a long-standing practice well known by the people living in the area [4]. For organizational reasons the Andromeda study is conducted simultaneously with another investigation, the Proteus study (NCT02590315), a randomized controlled trial aimed at comparing the performance of digital breast tomosynthesis (DBT) with those of standard digital mammography (DM). The study duration is planned for three years. Enrolment started in July 2015 and by the end of the recruitment phase (December 2017) about 21,000 women are expected to be included in the study. The women cohort will be followed up for additional ten years after the study ending through the screening archives to observe the onset of new BC cases.

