### Enrolment

At the time of BC screening appointment, all eligible women are offered to participate in both the Andromeda and the Proteus trials. In Fig. 1 the study flow is reported. After full explanation of the study protocols, a member of the research group obtains written informed consent from each participant (for one or for both studies). Women are reassured that non participation will not impact on their screening path.

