**Fig. 1 Fig1:**
[figure not shown]
The Andromeda Study

Women who agree to participate in Andromeda are asked to fill in a short risk questionnaire (SRQ - Additional file 1) to collect information on general BC risk factors (reproductive and BC family history, previous breast biopsies, basic physical activity level, body mass index and alcohol consumption), immediately at the enrolment desk.

In addition, they are asked to fill in a long risk questionnaire (LRQ - Additional file 2) on diet, physical activity, smoking habits, general state of health and psychological distresses (sections on physical activity and on dietary habits were modified from the EPIC questionnaires [25], the section on psychological distresses was taken from the Brief COPE questionnaire [26]). Women are also invited to undergo anthropometric measurements (height, weight, body composition, and waist circumference) and to provide a blood sample for serum, plasma and buffy-coat storing. Blood specimens are aliquoted, processed and stored at −80 °C. These last procedures can be performed at the time of the examination or at a later date, to be agreed with the woman; fasting is not required.

Mammograms derive either from DM or from DBT (according to the Proteus trial randomization) and are read by two expert radiologists. Breast density is calculated during breast examination, through a specific algorithm [27] and it is classified into categories by means of the Breast Imaging Reporting and Data System (BI-RADS) [28].

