### Statistical power and analysis

All the data collected through the SRQ will be used to obtain the risk estimates based on a risk prediction model that has been developed for the Italian population and validated on an independent cohort of Italian women (Petracci score) [32].

This information, along with the information on breast density, lifestyle related risk, polygenic risk score from miRNAs and SNPs will be modeled in respect of BC risk factors onset.

As they are determined on the same subjects, among women with abnormal mammography, the most efficient estimate of the ratio between relative (positive vs negative) positive predictive values (PPV) ratios, for any couple of the above factors is given by:$$ PPV\; ratios=\frac{cancers\;\left(\kern0em positive to factor1\; but\; not to factor2\right)\kern0.5em \times \kern0.5em non cancers\;\left(\kern0em positive to factor2\; but\; not to factor1\right)}{cancers\;\left(\kern0em positive to factor2\; but\; not to factor1\right)\kern0.5em \times \kern0.5em non cancers\;\left(\kern0em positive to factor1\; but\; not to factor2\right)} $$

Assuming that 40% of 21,000 enrolled women have a dense breast, 20% a certain Petracci score, 50% a lifestyle risk and 20% a given miRNA, that 11‰ of study women carry BC and that the overall PPV of mammography is 20%, some 100–120 discordant cancers and 640–740 discordant women with abnormal mammography but no cancer are expected for the considered couples of factors. Under these assumptions, the study has about 80% power to reject (alpha = 0.05) the null hypothesis that the relative PPV ratio equals 1 if its true value is at least 1.8–2.0, depending on the couple of factors considered.

To calculate the sample size necessary for biomarkers pivotal evaluation (expressed on a continuous scale), minimally acceptable and desirable levels of typical performance measures of interests, such as the true-positive rate (TPR) and the false positive rate (FPR) have been defined. For general population screening, the FPR must be quite low to avoid huge numbers of people undergoing unnecessary costly medical procedures. Thus a maximally acceptable false-positive rate (FPR0) of 4% (the minimally acceptable specificity is therefore 96%) and a minimally acceptable sensitivity of 80% (TPR0) were hypothesized. The null hypothesis to be rejected is the following: H0: TPR0 ≤ 0.80 or FPR0 ≥ 0.04.

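### The PPV-ratio estimator has no stratum for mammography technique, so comparisons of breast density with another factor would be biased if DM and DBT differ in both measured density and PPV

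*Protocol article*

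**What the plan says.** **Technique.** The text with Fig. 1 (Enrolment) states: "Mammograms derive either from DM or from DBT (according to the Proteus trial randomization"). Study setting describes Proteus as "a randomized controlled trial aimed at comparing the performance of digital breast tomosynthesis (DBT) with those of standard digital mammography (DM").

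**Consent.** Under Enrolment, a member of the research group "obtains written informed consent from each participant (for one or for both studies"). Andromeda can therefore be joined without Proteus.

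**Density.** "Breast density is calculated during breast examination, through a specific algorithm [27] and it is classified into categories", using BI-RADS. The article does not say whether the algorithm gives comparable results on DM and DBT.

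**Estimator.** Statistical power and analysis defines, "among women with abnormal mammography, the most efficient estimate of the ratio between relative (positive vs negative) positive predictive values (PPV) ratios", for any pair of factors. The printed formula multiplies cancers positive to factor 1 only by non-cancers positive to factor 2 only, and divides by the product of the other two discordant counts. It has no index for technique. Planning uses one density prevalence ("Assuming that 40% of 21,000 enrolled women have a dense breast"), one overall PPV of 20% and one cancer rate of 11 per 1,000.

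**Indicators.** Study aims lists, as a secondary objective, "risk group-specific screening indicators (i.e., detection rate, recall rate and benign/malignant surgical biopsy ratio"). No analysis method is given for these, and technique is not mentioned.

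**The concern.** The formula compares how discordant women split between two factors, in cancers and in non-cancers. Because both factors are measured on the same woman, it looks protected from confounding. That protection does not extend to a variable that changes one factor's reading and also changes the odds of cancer among the women analysed.

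Technique can be such a variable for density. If DM and DBT class different shares of women as dense, and an abnormal DM film carries a different PPV from an abnormal DBT film, technique is associated with both sides of the cross-product. Collapsing over it then distorts the ratio. Randomisation does not settle this, for three reasons:

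- a shift in measured density is an effect of technique on the measurement, which randomisation does not remove;
- the analysis is restricted to women with abnormal mammography, a status that itself depends on technique;
- women who consent to Andromeda alone fall outside the Proteus randomisation.

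At stake are the comparisons of density with the Italian risk score, with lifestyle and with miRNA, which belong to the first main aim.

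**Working it through.** **1. The plan's own figures.** Inputs from Statistical power and analysis: 21,000 women, 11 per 1,000 with cancer, PPV 20%.

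- Cancers: 21,000 × 0.011 = 231.
- Abnormal mammograms: 231 / 0.20 = 1,155.
- Non-cancers among them: 1,155 − 231 = 924.
- Discordant share for independent factors with prevalences p and q: p(1−q) + q(1−p). Density (40%) with a 20% factor: 0.4 × 0.8 + 0.2 × 0.6 = 0.44. Density with lifestyle (50%): 0.50.
- Discordant cancers: 231 × 0.44 = 102 and 231 × 0.50 = 116, within the stated 100–120.
- Discordant non-cancers: 924 × 0.44 = 407 and 924 × 0.50 = 462, below the stated 640–740. This mismatch is a separate matter. The bias below depends on proportions, so I use the counts that follow from a PPV of 20%.

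**2. Set-up for the bias (assumed).** Split the 1,155 abnormal films equally, 577.5 per technique. Let technique k have density prevalence p_k and PPV v_k. The comparator factor has prevalence q = 20%, independent of density. The true ratio is 1 within each technique. The cells are:

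- cancers, density only: 577.5 · v_k · p_k · (1−q)
- cancers, comparator only: 577.5 · v_k · (1−p_k) · q
- non-cancers: the same two with (1−v_k) in place of v_k.

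**3. Central case.** Technique A: 45% dense, PPV 15%. Technique B: 35% dense, PPV 25%.

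| Cell | A | B | Pooled |
|---|---|---|---|
| Cancers, density only | 31.2 | 40.4 | 71.6 |
| Cancers, comparator only | 9.5 | 18.8 | 28.3 |
| Non-cancers, density only | 176.7 | 121.3 | 298.0 |
| Non-cancers, comparator only | 54.0 | 56.3 | 110.3 |

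Pooled ratio: (71.6 × 110.3) / (28.3 × 298.0) = 0.94. Within A and within B the ratio is 1.00, so the Mantel-Haenszel ratio is 1.00.

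**4. Range, true ratio 1.** Every technique-specific figure is an assumption.

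| Density gap | PPV pair | Pooled ratio | Direction reversed | Mantel-Haenszel |
|---|---|---|---|---|
| 5 points | 17% / 23% | 0.98 | 1.02 | 1.00 |
| 10 points | 15% / 25% | 0.94 | 1.07 | 1.00 |
| 15 points | 15% / 30% | 0.87 | 1.15 | 1.00 |
| 20 points | 12% / 28% | 0.81 | 1.23 | 1.00 |

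The 5-, 10- and 20-point rows come out the same with a 50% comparator. A second grid anchors DM at the plan's values (40% dense, PPV 20%) and varies DBT over 25–35% dense, PPV 25–30% and a 25–50% share of films. It gives 0.91 to 0.99.

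**5. When there is no bias.** If density prevalence or PPV is equal in the two techniques, the pooled ratio stays at 1.00 when the true ratio is 1.

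**6. At the plan's target effect.** A true 1.8 becomes 1.62 to 1.78 in the anchored grid, and 1.55 or 2.04 in the 15-point case. If only density differs, it becomes 1.77 to 1.80.

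**7. Against sampling error.** With no technique difference the four cells are about 74, 28, 296 and 111. The standard error of the log ratio is √(1/74 + 1/28 + 1/296 + 1/111) = 0.25. The central bias, ln 0.94 = −0.06, is about a quarter of that. The largest, ln 0.81 = −0.21, is about 0.85 of it.

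**8. Precision cost of stratifying.** In the central case the standard error of an inverse-variance stratified log ratio is 0.251, against 0.248 pooled, about 1% more. In the 20-point case it is 0.257 against 0.248, about 4% more.

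**The case against.** The strongest objection is that this is a condensed article. A formula printed in a power section does not forbid stratified use, the text also says the factors will be modelled, and strata are commonly fixed in the full protocol or analysis plan. This holds fully for detection, recall and biopsy ratio. A reader might infer that those are to be pooled over technique, but the article only lists them as objectives and gives no method. It holds less well for the PPV ratio, where the article writes out a specific estimator, calls it the most efficient one, and plans it with a single PPV and a single density prevalence.

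The second objection is that the bias needs two facts the article does not supply. That Proteus compares the techniques does not show that PPV differs. The article also does not say which image the density algorithm uses in the DBT arm, so a density gap by technique is an assumption, as is the premise that density is read from the woman's own study film. This stands, and makes the point conditional.

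Third, the scope is limited. The score, lifestyle and miRNA are not image-derived, and among randomised women they are balanced by technique at enrolment, although selection to abnormal films could still differ. The mechanism shown here concerns density pairs.

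Fourth, the central bias is small beside the sampling error and the target ratios of 1.8–2.0. That also stands. It argues for a modest change, not for leaving the formula as it is, since the better estimator costs almost nothing.

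**Conclusion.** The point holds in a conditional form. The stated estimator ignores a known two-level source of variation that the sponsor's own concurrent trial is testing, and optional consent means that randomisation need not cover every participant. If technique shifts both measured density and PPV among abnormal films, density comparisons are biased. The bias is roughly 1–9% of a true ratio of 1 under the anchored moderate assumptions, and about 13–23% in either direction under large ones. At a true ratio of 1 it is zero if either quantity is equal across techniques. All technique-specific inputs are assumed.

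Two stronger readings are not supported. The documents do not establish that the density results will be biased. Nor do they show that overall screening indicators would describe neither technique: an overall rate describes the mix of techniques actually used, and it departs from the technique-specific rates only if those differ. For scale, with half the women on DBT, an overall detection rate of 11 per 1,000 would be 10.0 and 12.0 if the DBT-to-DM ratio were 1.2 (an assumed value).

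**What to change.** - In Statistical power and analysis, state that the PPV ratio is computed within DM and within DBT and combined as a Mantel-Haenszel common ratio, or that technique enters the equivalent regression as a stratum.
- State whether the density algorithm gives comparable classifications on DM and DBT.
- Keep women who consented to Andromeda only identifiable within the technique strata.
- Report detection rate, recall rate and benign/malignant biopsy ratio by risk group overall and, descriptively, by technique.

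**Cost.** The change is one of analysis wording, provided technique is recorded for each woman, which seems likely but is not stated. The common ratio uses all discordant women, and its standard error rises by about 1% in the central case and 4% in the 20-point case. Technique-specific estimates are less precise and should be labelled so. With half the stated discordant counts, a PPV ratio in one technique alone has 32–54% power at 1.8 and 40–68% at 2.0, for density against the risk score and density against lifestyle (two-sided 0.05 assumed). The common ratio should therefore carry the inference.

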### Biomarkers analysis

The Andromeda study includes molecular analyses to evaluate circulating miRNAs and SNPs that will be performed blindly on an appropriate case-control sample extracted from the cohort of enrolled women, as soon as a minimum number of BC cases will be reached. Blinding allows avoiding that knowledge of subject’s outcome status affect the interpretation of an assay result or the care with which the specimen is handled. The prospective specimen collection plus retrospective blinded-evaluation (PRoBE) design assumed here has been proposed by Pepe et al. [29] as a good practice to follow for the pivotal evaluation of biomarker accuracy.

The selected miRNAs come from two consolidated studies [20, 21], and are suited to the screening nature of the Andromeda study.

In more detail the biomarkers to be analyzed are the following:Circulating total RNA extraction from plasma samples will be carried out with miRNeasy serum/plasma minikit (Qiagen) with minor modifications of the Exiqon protocol, implying use of a RNA carrier (batteriofage MS2 RNA, Roche Diagnostics®) to promote RNA precipitation. Cel-miR-139 will be used as spike-in control to check extraction yield and to normalize data. RNA samples will be purified on membranes and eluted with nuclease free water and stored at −80 °C. We will carefully evaluate the presence of haemolysis in our analysis and exploit our huge sample cohort to validate previous results on an independent dataset.RT-qPCR analysis of selected markers (genes, microRNAs, lncRNAs)Total RNA samples will be reverse-transcribed and amplified with specific assays for cel-miR-39, hsa-miR-1228, hsa-miR-145, hsa-miR-451, hsa-miR-222, hsa-miR-18a, hsa-miR-181a and analyzed on a qPCR apparatus with specific dedicated software. Every RNA samples will be analyzed in triplicate. Normalization of expression data will be carried out using hsa-miR-1228 [30] and cel-miR-39 as normalizers. As for SNPs also for miRNAs research findings are continuously updated, so they will be selected considering the most recent findings at the time of their extraction [31].SNP genotypingGenomic DNA will be extracted from buffy coat with High Pure PCR Template preparation kit (Roche Diagnostics®). 77 SNPs described in Mavaddat et al. [18] will be evaluated using the Personal Genome Machine (Ion Torrent) NGS apparatus.

### Statistical power and analysis

All the data collected through the SRQ will be used to obtain the risk estimates based on a risk prediction model that has been developed for the Italian population and validated on an independent cohort of Italian women (Petracci score) [32].

This information, along with the information on breast density, lifestyle related risk, polygenic risk score from miRNAs and SNPs will be modeled in respect of BC risk factors onset.

As they are determined on the same subjects, among women with abnormal mammography, the most efficient estimate of the ratio between relative (positive vs negative) positive predictive values (PPV) ratios, for any couple of the above factors is given by:$$ PPV\; ratios=\frac{cancers\;\left(\kern0em positive to factor1\; but\; not to factor2\right)\kern0.5em \times \kern0.5em non cancers\;\left(\kern0em positive to factor2\; but\; not to factor1\right)}{cancers\;\left(\kern0em positive to factor2\; but\; not to factor1\right)\kern0.5em \times \kern0.5em non cancers\;\left(\kern0em positive to factor1\; but\; not to factor2\right)} $$

Assuming that 40% of 21,000 enrolled women have a dense breast, 20% a certain Petracci score, 50% a lifestyle risk and 20% a given miRNA, that 11‰ of study women carry BC and that the overall PPV of mammography is 20%, some 100–120 discordant cancers and 640–740 discordant women with abnormal mammography but no cancer are expected for the considered couples of factors. Under these assumptions, the study has about 80% power to reject (alpha = 0.05) the null hypothesis that the relative PPV ratio equals 1 if its true value is at least 1.8–2.0, depending on the couple of factors considered.

To calculate the sample size necessary for biomarkers pivotal evaluation (expressed on a continuous scale), minimally acceptable and desirable levels of typical performance measures of interests, such as the true-positive rate (TPR) and the false positive rate (FPR) have been defined. For general population screening, the FPR must be quite low to avoid huge numbers of people undergoing unnecessary costly medical procedures. Thus a maximally acceptable false-positive rate (FPR0) of 4% (the minimally acceptable specificity is therefore 96%) and a minimally acceptable sensitivity of 80% (TPR0) were hypothesized. The null hypothesis to be rejected is the following: H0: TPR0 ≤ 0.80 or FPR0 ≥ 0.04.

The sample size required with an 80% power (alpha = 5%) and assuming desirable true-positive rate and false-positive rate of TPR1 = 0.90 and FPR1 = 0.05, respectively, was of 179 cases and 537 controls. Sample size computation was based on theory on the Receiver Operating Characteristic (ROC) curve.

Assuming an annual BC detection rate (DR) of 0.006 in the first year and 0.005 in the second year of the study (therefore the biennial DR considered was 0.011) a total of 233 case patients in the first two years of the study are expected to be observed, thus exceeding the 179 required. These estimates are based on DRs observed in the previous years in the same centers considered in this study (Turin, Biella) [4]. Thus, the molecular analyses will be performed on 233 cases and 699 matched controls. For each case, three control subjects will be selected from the cohort of women, on the basis of the following criteria: no history of cancer, similar age at enrolment (within 5 years), similar race, availability of blood sample, similar date of blood draw.

Moreover, circulating miR-18a, miR-181a, and miR-222 levels - derived from the sister study cohort [21] - on plasma collected from all the women enrolled that have at least one first degree relative with BC will be assessed. The estimated number of this subgroup is 1800 women, 40 of which are expected to develop BC within 18 months, and will therefore belong to the case group.

To assess the predictive ability of the considered criteria (i.e., breast density, absolute risk of developing BC and, lifestyles) in identifying groups of women with different risk levels, the positive and negative predictive values and ratios of predictive values (PPV and PPV ratios) will be calculated for each criterion.

The discrimination ability of single biomarkers will be evaluated by means of the ROC curves, whereas to test if biomarker levels are significantly higher or lower in cases and controls, logistic regression models will be used. To evaluate the association between women’s characteristics or tumor features and biomarker level, linear regression models will be adopted.

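### The formula labelled a PPV ratio is an odds ratio among recalled women, so the detectable 1.8–2.0 is on the odds scale and does not by itself measure cancer risk in all screened women

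*Protocol article*

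**What the plan says.** In the protocol article, Study aims gives the purpose of the comparison, with PPV as the yardstick: "In order to define groups of women characterized by different BC risk, the above mentioned criteria will be assessed and compared in terms of positive" (the sentence goes on to name PPV). Statistical power and analysis then restricts that comparison to women with an abnormal mammogram and names its target: "among women with abnormal mammography, the most efficient estimate of the ratio between relative (positive vs negative) positive predictive values (PPV) ratios". It gives one expression, "for any couple of the above factors is given by" the product of cancers positive to factor 1 only and non-cancers positive to factor 2 only, divided by the product of the two opposite cells. The article calls the result a PPV ratio.

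The planning assumptions follow: "Assuming that 40% of 21,000 enrolled women have a dense breast, 20% a certain Petracci score, 50% a lifestyle risk and 20% a given miRNA", and "that 11‰ of study women carry BC and that the overall PPV of mammography is 20" per cent. From these the article concludes that "some 100–120 discordant cancers and 640–740 discordant women with abnormal mammography but no cancer are expected", and that "the study has about 80% power to reject (alpha = 0.05) the null hypothesis that the relative PPV ratio equals 1" when the true value is at least 1.8–2.0, depending on the pair.

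**The concern.** A PPV is cancers divided by cancers plus non-cancers. The printed expression divides cancers by non-cancers in each discordant group, so it compares odds. Odds and proportions nearly agree when the outcome is rare, but among recalled women the plan assumes that one in five has cancer. A reader who takes the reported figure, or the detectable 1.8–2.0, as a ratio of PPVs will think the criteria differ more than they do.

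The second issue concerns a different target. The aim is to group screened women by cancer risk, but the formula sees only women who were recalled. If a criterion also changes the chance of a false-positive recall, the non-cancers in the formula shift with it, and the ratio mixes cancer risk with recall. This matters because the comparison is meant to inform stratified screening.

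**Working it through.** **Notation.** c10 and n10 are cancers and non-cancers positive to factor 1 only; c01 and n01 are those positive to factor 2 only. All are recalled women.

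**The formula.** (c10 × n01)/(c01 × n10) = (c10/n10)/(c01/n01), a ratio of odds. The discordant-cell PPV ratio is [c10/(c10+n10)]/[c01/(c01+n01)].

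**The plan's own counts.** Inputs are from Statistical power and analysis; independence of the factors is my assumption.
- Cancers: 21,000 × 0.011 = 231.
- Recalled women: 231/0.20 = 1,155, so 1,155 − 231 = 924 without cancer.
- Discordant fraction p(1−q) + q(1−p): 0.44 to 0.50 for every pair except Petracci with miRNA (0.32).
- Discordant cancers: 231 × 0.44 = 102 to 231 × 0.50 = 116, in line with the stated 100–120 (74 for Petracci with miRNA).
- Discordant non-cancers: 924 × 0.44 = 407 to 924 × 0.50 = 462, not the stated 640–740. That range needs 640/0.44 = 1,455 to 740/0.50 = 1,480 non-cancers, a PPV of about 13.5–13.7%. Both PPVs are therefore carried below.
- Detectable ratio (80% power, two-sided 0.05, the rarer factor being the stronger, same exception): 1.79–1.93 with 924 non-cancers and 1.75–1.88 with about 1,470. This broadly matches 1.8–2.0, but on the odds-ratio scale. If the commoner factor is the stronger, the values run from 1.8 to 2.7.

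**Odds against PPV, density (40%) and lifestyle (50%).** n10 = 924 × 0.20 = 184.8; n01 = 924 × 0.30 = 277.2; c10 + c01 = 115.5.
- Formula value 1.8: c10 = 63.0, c01 = 52.5. PPVs are 63.0/247.8 = 0.254 and 52.5/329.7 = 0.159; ratio 1.60.
- Formula value 2.0: c10 = 66.0, c01 = 49.5. PPVs are 66.0/250.8 = 0.263 and 49.5/326.7 = 0.152; ratio 1.74.

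Across all pairs the discordant-cell ratios are 1.58–1.63 and 1.71–1.78. A logistic model for recalled women, calibrated to 20% PPV and with the second factor neutral, gives ratios of relative (positive vs negative) PPVs of 1.57–1.60 and 1.70–1.75. Taken together, the formula is about 11–18% larger (for example 1.80/1.63 and 2.00/1.70). At a PPV of about 13.6% the model gives 1.64–1.66 and 1.79–1.82, so 8–12%.

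**Restriction to recalled women (illustration; the recall multiples are assumed).** Factor 1 (40% prevalence) doubles cancer risk, 15.7 against 7.9 per 1,000; factor 2 (20%) is neutral. Cancers are 132 in factor-1-positive and 99 in factor-1-negative women, so c10 = 132 × 0.8 = 105.6 and c01 = 99 × 0.2 = 19.8. The 924 false positives are shared out according to the multiple.

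| False-positive recall multiple for factor 1 | n10 | n01 | Formula |
|---|---|---|---|
| 1 | 295.68 | 110.88 | 2.00 |
| 1.5 | 369.6 | 92.4 | 1.33 |
| 2 | 422.4 | 79.2 | 1.00 |
| 2.5 | 462.0 | 69.3 | 0.80 |

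**The case against.** The best defence is that recalled women without cancer can serve as controls. If false-positive recall is unrelated to the factors, n01/n10 mirrors the cohort and the formula returns the cohort relative risk, 2.00 in the first row of the table. Against that target it does not exaggerate, and a true PPV ratio would be the attenuated figure. This stands. A reader might infer that the formula is inflated against every target; it is inflated only as a measure of PPV among recalled women. But PPV is the target the article names, and the condition on recall is not stated.

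Four other limits stand.
- Among recalled women, an odds ratio of 1 and a discordant-cell PPV ratio of 1 are the same null hypothesis, so the test is sound.
- A reader might infer that the mislabelling leaves the study underpowered. It works the other way: a true relative PPV ratio of 1.8–2.0 corresponds to a formula value of about 2.1–2.5, which is easier to detect.
- A reader might infer that breast density will show no difference, or that the ranking of criteria will be corrupted. The documents give no recall figure by factor, so the table shows only what can happen.
- Study aims already plans detection and recall rates by risk group, and Statistical power and analysis plans predictive values for each criterion. A doubled risk could therefore still be seen elsewhere; the fault lies in the named pairwise comparison and its power sentence.

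Finally, which population should carry the main comparison is partly a choice of estimand. Cancers per screened woman cannot be computed directly for miRNA or SNP pairs, because those markers are not measured across the whole cohort.

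**Conclusion.** The point holds in two separate parts.

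First, the expression is an odds ratio under a PPV label. At the assumed 20% PPV, the stated detectable 1.8–2.0 is about 1.6–1.8 as a PPV ratio, an excess of 11–18%, or 8–12% at a PPV near 13.6%. For ratios below 1 the distortion runs the other way, so in general the figure lies too far from 1. These sizes rest on independent factors and the plan's own prevalences.

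Second, the comparison speaks to cancer risk in all screened women only if false-positive recall does not vary with the factor. The article neither states nor excludes this, and how far it fails is unknown from the documents.

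Neither part undermines the test of equality among recalled women. The change is worth making because the reported size is what would be read when choosing criteria for stratified screening.

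**What to change.** 1. Either name the expression an odds ratio among recalled women and restate the detectable 1.8–2.0 as odds ratios (about 1.6–1.8 as PPV ratios), or replace it with an actual ratio of relative PPVs, using an estimator and confidence interval suited to paired data. Reconcile the 640–740 non-cancers with the 20% PPV when restating.
2. For density, Petracci score and lifestyle, also compare cancers per screened woman between the two discordant groups, among women with both factors recorded. Base conclusions about risk stratification on that comparison. It uses the detection-rate data already planned in Study aims.
3. For pairs involving miRNA or SNPs, keep the odds ratio, label it as such, and say which non-cancer women it uses, since the controls are drawn from the cohort.
4. State that the recalled-women comparison reflects cohort risk only if false-positive recall is unrelated to the factor, and refer to the planned recall rates by risk group as the check.

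The cost is analysis wording, one added analysis on data the study already sets out to collect, and ratios that look smaller. Women who did not complete the lifestyle questionnaire may drop out of some pairs.
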